### Enrollment criteria

Young women and men will be eligible for the study if they meet the following criteria:

• Age 16-35 years.

• Diagnosis of RA, according to the revised 1987 ACR criteria for at least 6 months.

• Concomitant use of disease modifying antirheumatic medications (hydroxychloroquine, sulfasalazine, methotrexate, leflunomide, etc.) and/or biologic agents (infliximab, etanercept, adalimumab, abatacept, rituximab, anakinra) is permitted provided that the dose(s) have been stable for 8 weeks prior to screening, and subjects may reasonably be expected to remain on stable doses throughout the study.

• Concomitant use of NSAIDs and low dose corticosterioids (e.g., prednisone at doses of 10 mg/day prednisone or equivalent) is permitted provided that the dose(s) have been stable for 4 weeks prior to screening, and subjects may be expected to remain on stable doses throughout study duration.

• Disease activity, as defined using a 28 joint count by ≥ 5 tender joints, ≥ 5 swollen joints, and one of the following: Erythrocyte Sedimentation Rate (ESR) ≥ 28 mm/hour, C-reactive protein (CRP) ≥ 1.5 mg/dL, duration of a.m. stiffness ≥ 45 minutes.

• Able and willing to give written informed consent and comply with the requirements of the study.

• Ability to speak and understand English.

### Exclusion criteria

Patients will be excluded from the study based on the following criteria:

• Intra-articular steroid injections within 4 weeks of screening.

• Treatment with any investigational agent within 8 weeks of screening or 5 half-lives of the investigational drug (whichever is longer).

• History of drug, alcohol, or chemical abuse within 6 months prior to screening.

• Any other disease, metabolic dysfunction, physical examination finding, or clinical laboratory finding giving reasonable suspicion that might affect the interpretation of the results or render the patient at high risk from treatment complications.

• Inability to comply with study and follow-up procedures.

• Currently pregnant.

• Previous practice of Iyengar yoga within the past three months.

• Inability to speak and understand English.

According to the Power/Sample Size calculations outlined below, we will recruit 35 patients each for the IYP and control conditions. After accounting for our projected attrition rate of 20%, we estimate there will be roughly 28 treatment completers in each condition. To accommodate 56 participants during the 36-month study period, we plan to conduct 4 initial IYP groups and 4 initial control groups, with approximately 8 patients in each group.

### Sample Size Determination and Power Analysis

A power analysis was conducted to determine the appropriate sample size. Using a pre-test post-test for randomized groups, calculating power of the interaction of treatment by time, the sample size estimate is a total sample of 54, or 27 subjects per group (at a 0.05 significance level, 80% power for a medium effect size). We calculated a medium effect size given that our recent single-arm pilot study found an effect size of .46 (Cohen's d) for the HAQ, our arthritis-specific primary outcome measure. Assuming a 20% attrition rate that is consistent with our previous yoga studies, we will recruit 35 participants for each group (total n = 70).

### Randomization

Before completing the baseline assessments, participants will be randomly allocated to the intervention or control group. The research team will assign the patient to the groups using randomization schedules generated by UCLA Biomathematics for group assignment in blocks of 4. As each patient is enrolled, he or she will be assigned to the next number on the list and the associated condition, yoga or usual care.

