### Design

A randomized control trial (RCT) design will be used to examine the impact of IYP for adolescents and young adults aged 16-35 years with RA on the primary outcomes of general and arthritis-specific functioning, and the secondary outcomes of DAS28, pain and mood.

The overall design of the study is depicted in Figure 2 below. After participants have completed the telephone screening and meet the study's eligibility criteria, they will be randomized into the IYP or usual care control group. All participants will be asked to fill out consent forms before their initial medical assessment, which includes a phlebotomy, measurement of blood pressure/resting heart rate, and a joint count conducted by a physician who will be kept unaware of group assignment. Before the medical assessment, a research assistant will send a link to the questionnaires for participants who choose to complete them online. A hard copy of the questionnaires will be taken to the medical assessment if the participant chooses to complete the paper-based version in a private medical office.

Those assigned to the IYP will then engage in the 6-week program; they will repeat the baseline assessments immediately following treatment and again at a two-month follow-up. Patients initially assigned to the wait-list group will continue their usual care. Both the yoga and control groups will either receive weekly phone calls or e-mails to monitor symptoms, medication use and physical activity. After 6 weeks, control participants will be re-assessed to ensure that they still meet study eligibility criteria; those that continue to meet criteria will then take part in the IYP. Following the IYP, participants will then repeat the baseline assessments at post-treatment and two-month follow-up.

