### Recruitment

Participants will be recruited from the UCLA Division of Rheumatology, the UCLA pediatric rheumatology program, private medical offices of rheumatologists, UCLA Student Psychological Services, health newsletter ads, the young adult support network of the Southern California Chapter of the Arthritis Foundation, and community resources, such as library and other public notice boards, as well as websites, such as Craigslist. The UCLA Division of Rheumatology has a current patient population of 150 individuals with RA who are 16-21 years of age. The UCLA pediatric rheumatology program sees 100 patients with arthritis 16 years and older. Private practice rheumatologists in Los Angeles who have agreed to assist with our project can refer an additional 200 patients with RA in our targeted age range. The Southern California chapter of the Arthritis Foundation will help us recruit from their pool of several hundred RA patients who regularly receive their email announcements and mailed bulletins. In all, we anticipate being able to recruit from a pool of over 500 individuals with RA in the targeted age-range.

The project director will meet with health care providers, staff and support group leaders to inform them about the project and to ask them to distribute and post flyers about the study. The flyers will describe the project and ask interested volunteers to call the project manager to establish their eligibility. Additionally, a lay advisory board comprised of young adults with RA will be formed and consulted with in the development of recruitment materials as well as in the finalization of the protocol and research instruments.

Effort will be made to recruit the patient sample to be broadly representative of the general population of RA patients in the targeted age range. Epidemiological data suggest that the racial composition of RA in the U.S. is approximately 84.4% non-Hispanic whites, 8.3% non-Hispanic blacks, 2.3% Mexican American and 5% other [50]. Women are between 60-75% more likely to experience RA than men [50,51]. We will also attempt to recruit patients to reflect the demographic composition of the Greater Los Angeles area which is estimated to be approximately 75% White, 13% Asian, 10% African-American, 1% American Indian/Alaska Native, and 1% Native Hawaiian/Other Pacific Islander; ethnic makeup will be 45% Hispanic and 55% Non-Hispanic.

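### Randomisation is placed before the self-reported baseline and before any examination that could confirm eligibility

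*Protocol article*

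**What the plan says.** The Randomization section gives the order directly: "Before completing the baseline assessments, participants will be randomly allocated to the intervention or control group". The Design section agrees: "After participants have completed the telephone screening and meet the study's eligibility criteria, they will be randomized". It then describes the initial medical assessment (blood draw, blood pressure and heart rate, joint count) and the questionnaires, which go out online beforehand or are brought to that visit on paper. Masking is stated for one person only, in "a joint count conducted by a physician who will be kept unaware of group assignment".

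On consent, the Design section says: "All participants will be asked to fill out consent forms before their initial medical assessment". It does not place consent before or after allocation.

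On eligibility, Recruitment says that flyers will "ask interested volunteers to call the project manager to establish their eligibility". Enrollment criteria requires "Disease activity, as defined using a 28 joint count by ≥ 5 tender joints, ≥ 5 swollen joints", plus one of ESR, CRP or morning stiffness above a threshold. Exclusion criteria adds a judgement-based exclusion that can rest on examination or laboratory findings.

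On allocation, the research team assigns each enrolled patient to the next number on a list, using "randomization schedules generated by UCLA Biomathematics for group assignment in blocks of 4".

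The baseline is used in several places. Primary analyses tests a group-by-time interaction (baseline against post-treatment) on SF-36, PDI and HAQ, and pools the arms for the follow-up analysis if they do not differ significantly at baseline. Preliminary analyses uses baseline tests to choose covariates and to judge whether randomisation succeeded.

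**The concern.** A baseline is useful because allocation cannot have influenced it. Here it is collected after allocation, by self-report, from people who may know their arm. Someone about to start classes and someone told to wait may answer questions on pain, disability and quality of life differently. The primary test cannot separate such a difference from a treatment effect on change. The same values also decide covariates and pooling, so a distortion would spread to those steps.

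The second problem is a conflict between sections. Eligibility is said to be met at randomisation, but a telephone call cannot supply a 28-joint count or a laboratory result. If the medical assessment is where these are first obtained, some people could prove ineligible after being randomised. Removing them could then depend on the arm, and keeping them would leave the entry criteria unapplied.

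**Working it through.** There is no stated figure to reproduce; the main check is one of sequence. Two short calculations show scale.

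**1. Sequence**

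| Step | Where it is placed | Source |
|---|---|---|
| Telephone screen | before randomisation | Design |
| Eligibility met | asserted before randomisation | Design |
| Randomisation | before the baseline assessments | Randomization |
| Consent | before the medical assessment; not placed relative to randomisation | Design |
| Joint count, blood draw | initial medical assessment, at baseline | Design |
| SF-36, PDI, HAQ | around that assessment, at baseline | Design |

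Two sections independently give the order randomisation, then baseline. Keeping the physician at the initial assessment unaware of assignment also makes sense only if assignment already exists. No examination or blood test is described before randomisation.

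**2. How a baseline shift enters the primary test**

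With two time points, the group-by-time interaction is the between-arm difference in change. Let *b* be the between-arm reporting shift at baseline caused by knowing the arm, and *p* the same kind of shift at post-treatment. The bias in the estimate is *p* − *b*.

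- Shift at baseline only (*p* = 0): bias = −*b*, the whole shift.
- Shift that persists (*p* = *b*): bias = 0.
- Baseline used as a covariate: only the regression-slope fraction of *b* enters, so the bias is reduced but not removed.

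**3. Illustrative false-positive rate**

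Inputs: 28 completers per arm (text following Exclusion criteria) and a 0.05 significance level (Sample Size Determination), taken as two-sided. Assumed, because the document gives neither: pre-post correlation *r* of 0.5 or 0.7, and a baseline-only shift of 0.1, 0.2 or 0.3 SD. There is no true effect.

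SE of the difference in change = √(2(1 − r)) × √(2/28).

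- r = 0.5: 1.000 × 0.267 = 0.267
- r = 0.7: 0.775 × 0.267 = 0.207

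False-positive rate = 1 − Φ(1.96 − t) + Φ(−1.96 − t), with t = shift/SE.

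| Shift (SD) | r = 0.5 | r = 0.7 |
|---|---|---|
| 0.1 | 0.066 | 0.077 |
| 0.2 | 0.116 | 0.162 |
| 0.3 | 0.202 | 0.305 |

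A cross-sectional baseline comparison with 28 per arm also has SE √(2/28) = 0.267. It would therefore flag a 0.2 SD shift only about 12% of the time, so the planned check that randomisation succeeded would usually miss it.

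**4. Predictability of fixed blocks of 4 (secondary)**

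Over the six possible orders of two and two, the next assignment is certain with probability 0, 0, 1/3 and 1 at places one to four: (0 + 0 + 1/3 + 1)/4 = 1/3, or about 23 of 70. The best guess is right with probability (1/2 + 2/3 + 2/3 + 1)/4 = 0.708. Both figures require someone who has tracked every past assignment and knows where blocks begin.

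**The case against.** Several stronger readings are tempting, and the document does not support them.

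- **Consent follows allocation.** A reader might infer this from the order of sentences in Design. The text ties consent only to the medical assessment, and Randomization speaks of assigning patients as they are enrolled, which ordinarily implies consent. The flowchart is not available here. The timing is unstated and may be after allocation; no more can be said.
- **Ineligible people are found only after allocation.** Design asserts eligibility beforehand and later checks that controls still qualify, which implies an earlier confirmation. Clinic or referral records could have supplied the data, though the document does not say so and recruitment also uses public notices. What stands is the conflict between sections.
- **The team can see coming assignments.** Who holds the list and how it is concealed are details that an article commonly leaves to the full protocol. Silence is not a fault, and a fixed block of 4 is not in itself an error.
- **Any baseline shift biases the result in full.** Only a shift specific to baseline does so.
- **The bias can be stated as a share of the 0.46 pilot effect.** That figure is a single-arm HAQ effect size with no standardiser given. Setting an assumed between-arm shift against it would mix different quantities and extend a HAQ figure to SF-36 and PDI.

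There are also partial safeguards. The masked physician protects the joint count, completers are compared with non-completers, and an intention-to-treat analysis is planned. None of them protects a self-reported baseline. The carry-forward rule also has nothing to carry for someone lost between allocation and baseline. The article does not say when participants learn their arm, but nothing described keeps it from them until baseline is done.

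This is a preliminary study, which lowers the stakes. It still tests efficacy hypotheses on these three outcomes.

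**Conclusion.** The point holds for the stated order. Randomisation precedes an unmasked, self-reported baseline that feeds the primary test, the covariate choice and the pooling decision. The eligibility statement in Design also conflicts with the entry and exclusion criteria. Both rest on explicit text.

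The size of the bias is not known. The false-positive rates above depend on an assumed shift, an assumed correlation and a shift confined to baseline; the document also gives no basis for its direction. If participants learned their arm only after completing baseline, the reporting problem would disappear, but the plan does not provide for that. Consent timing is a matter for clarification, and block predictability is secondary. The order should be changed before enrolment, because no analysis can fully recover a baseline already affected by allocation.

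**What to change.** Re-order to: telephone pre-screen; consent; medical assessment and baseline questionnaires; eligibility confirmed against the enrolment and exclusion criteria; randomisation. UCLA Biomathematics, which already generates the schedule, should release each assignment only after the participant is logged as consented, eligible and baseline-complete. State the timing of consent explicitly, and reconcile Design with Enrollment criteria and Exclusion criteria on how and when eligibility is established. Secondarily, use varying block sizes that are not disclosed to the enrolling team.

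Cost: the planned sample size does not change. Participants learn their arm later, and the assessment visit must be finished before class groups are assigned. Some people will be examined and then found ineligible. The joint count and blood draw are already planned. CRP and morning stiffness are not named in the initial assessment, so they would need a stated source if used to qualify someone.

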### Recruitment

Participants will be recruited from the UCLA Division of Rheumatology, the UCLA pediatric rheumatology program, private medical offices of rheumatologists, UCLA Student Psychological Services, health newsletter ads, the young adult support network of the Southern California Chapter of the Arthritis Foundation, and community resources, such as library and other public notice boards, as well as websites, such as Craigslist. The UCLA Division of Rheumatology has a current patient population of 150 individuals with RA who are 16-21 years of age. The UCLA pediatric rheumatology program sees 100 patients with arthritis 16 years and older. Private practice rheumatologists in Los Angeles who have agreed to assist with our project can refer an additional 200 patients with RA in our targeted age range. The Southern California chapter of the Arthritis Foundation will help us recruit from their pool of several hundred RA patients who regularly receive their email announcements and mailed bulletins. In all, we anticipate being able to recruit from a pool of over 500 individuals with RA in the targeted age-range.

The project director will meet with health care providers, staff and support group leaders to inform them about the project and to ask them to distribute and post flyers about the study. The flyers will describe the project and ask interested volunteers to call the project manager to establish their eligibility. Additionally, a lay advisory board comprised of young adults with RA will be formed and consulted with in the development of recruitment materials as well as in the finalization of the protocol and research instruments.

Effort will be made to recruit the patient sample to be broadly representative of the general population of RA patients in the targeted age range. Epidemiological data suggest that the racial composition of RA in the U.S. is approximately 84.4% non-Hispanic whites, 8.3% non-Hispanic blacks, 2.3% Mexican American and 5% other [50]. Women are between 60-75% more likely to experience RA than men [50,51]. We will also attempt to recruit patients to reflect the demographic composition of the Greater Los Angeles area which is estimated to be approximately 75% White, 13% Asian, 10% African-American, 1% American Indian/Alaska Native, and 1% Native Hawaiian/Other Pacific Islander; ethnic makeup will be 45% Hispanic and 55% Non-Hispanic.

### Intervention

#### Iyengar Yoga Program (IYP)

IY is a traditional form of yoga taught in the lineage of BKS Iyengar, who is known for his prominent texts on yoga and innovative teaching techniques. Iyengar has developed specific methods of teaching therapeutic yoga practices to people with health problems [52-54]. IY is an ideal form of activity for people with RA, as the emphasis on alignment in this practice protects joints, is unlikely to irritate inflamed joints and involves sufficient movement to tap the beneficial effects of exercise. Young RA patients with fatigue, restricted motion and painful joints can perform postures with the support of props (blocks, bolsters, chairs, straps and blankets) that allow postures to be held without stress. Yoga postures are designed to promote circulation, stimulate the hormonal system and circulate lymph through body position and muscle activity. The use of props allows inverted postures to be held for long periods of time without fatigue so that the lymph is well circulated without strain. Challenging back bending postures designed to stimulate the adrenal glands can also be held for longer periods of time with the support of props. The poses to be included in this intervention are based on the teachings of BKS Iyengar. The poses include supine poses, passive backbends, standing poses, seated poses, forward bends and supported inversions. All will be done with use of props as needed (see Figure 3).

**Figure 3 F3:**
[figure not shown]
**Selected yoga poses**.

Yoga taught in the Iyengar tradition is known for an extensive teacher training program. Iyengar teachers study for at least seven years before being certified to work with students who have therapeutic needs. They must pass several certification tests before an impartial national board. These tests include teaching, performance of poses and breathing techniques, anatomy and therapeutic sequences. Because of this training, IY teachers across the country and around the world can accurately reproduce the IYP in this study.

The proposed IYP will be administered twice a week for 1.5 hours duration per session for 6 weeks. Due to the extensive time commitment required for the IYP, there will be no instructions for home practice, but neither will participants be discouraged from practicing at home. At the end of the 6-week IYP, those participants who ask for referrals to IY studios/teachers in the community will be given a list of referrals. All home practice as well as post-IYP yoga classes will be monitored during the weekly phone calls/e-mails and at the post-treatment and follow-up assessments; the extent of home practice will be evaluated in the analyses for its potential impact on outcome.

Should subjects experience a flare-up during the IYP, the research team will consult with the patient's rheumatologist and a modified version of the IYP will be offered to the subject consisting of restorative poses that do not place strain on the affected joints.

### Treatment administration

As illustrated in Figure 4, two streams of yoga classes will run concurrently to minimize the overall length of the study and to maximize the likelihood that yoga classes will be convenient for patients' schedules. For example, Stream 1 classes will be held on Mondays and Wednesdays, while Stream 2 classes will be held on Tuesdays and Thursdays. Stream 1 and Stream 2 will comprise the first Wave of patients (Wave 1). Upon the completion of Wave 1, a second wave of patients (Wave 2) will consist of two additional Streams of classes. A make-up class will be scheduled each week for any patient not able to attend their usual session. Thus, all patients should be able to receive the full course of IYP since classes will be run 5 days per week (e.g., make-up classes held on Fridays). We will make note of how many make-up classes each patient attends and test for possible differential effects due to missing regular classes. Patients in the control groups will be given the opportunity to take part in the IYP at the end of the 6-week control period. To increase patient safety and accurate practice of poses, IY classes will hold a maximum of 9 patients.

